## Abstract

This article reports the protocol of a single-arm exploratory study investigating the impact of singing on the brain activity of premature infants in the Neonatal Intensive Care Unit (NICU). The study focuses on how the differentiation of voices, as defined by the fundamental frequency (F0) shaped by biological sex and kinship, influences neurophysiological responses when measured by electroencephalography (EEG). Premature infants, who are highly sensitive to auditory stimuli, may benefit from music-based interventions; however, there is limited understanding of how voice variations between male and female caregivers, and whether they are biologically related, affect brain activity. Our protocol outlines a structured intervention where infants are exposed to singing by four facilitators – a male and a female music therapist, the mother, and the father – and includes two singing stages: a sustained note and a lullaby, both interspersed with silent periods to allow for baseline measurements. EEG recordings track brain activity throughout these sessions, followed by quantitative EEG (qEEG) analysis and thorough statistical computations (e.g., mixed-effects models, spectral power analysis, and post-hoc tests) to explore how these auditory stimuli influence brain function. Preliminary data from five infants show that maternal singing elicits the highest delta spectral power in all measured conditions except during the ‘lullaby song’, where paternal singing elicits the highest effects followed by the male music therapist and then the mother. These early findings highlight the potential influence of parental voices, particularly the fathers’ voice, on neonatal brain development, while the detailed study protocol ensures rigor and replicability, providing a robust framework for future research. (clinicaltrials.gov unique identifier: NCT06398912).

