#### Results – descriptive statistics.

In terms of the EEG analysis results for this dataset, the descriptive statistics for spectral power in the Delta frequency across different facilitators and conditions are detailed in Table 2 below. The highest mean spectral power was observed during maternal interventions, particularly in the ‘NoteA’ condition (Mean = 1381.3 *μ*V^2^, SD = 1794.5 *μ*V^2^), emphasizing the notable influence of maternal presence in general.

**Table 2 pone.0328211.t002:** Descriptive statistics for spectral power on delta frequency (in *μ*V^2^ for Mean and SD).

Facilitator	Condition	Mean	Standard Deviation	Coefficient of Variation (%)
[name]	NoteA	276.1	269.9	97.7
Father	NoteA	657.1	937.4	142.7
[name]	NoteA	273.6	129.5	47.3
Mother	NoteA	1381.3	1794.5	129.9
Total	NoteA	647.1	1047.2	161.8
[name]	Silence1	92.7	83.4	90
Father	Silence1	161.2	175.8	109.1
[name]	Silence1	339	308.7	91.1
Mother	Silence1	703.1	745.9	106.1
Total	Silence1	324	451.8	139.4
[name]	Silence2	114.8	162.3	141.4
Father	Silence2	148.7	103.3	69.4
[name]	Silence2	225.7	137.3	60.9
Mother	Silence2	218	168.8	77.4
Total	Silence2	176.8	141.6	80.1
[name]	Silence3	94.3	84.6	89.7
Father	Silence3	427.6	785.9	183.8
[name]	Silence3	378.3	538.1	142.2
Mother	Silence3	1020.7	1797.1	176.1
Total	Silence3	480.2	995.9	207.4
[name]	Song	79.1	76.2	96.4
Father	Song	574.2	920.8	160.4
[name]	Song	270.2	231.8	85.8
Mother	Song	213.4	185.7	87
Total	Song	284.2	482.5	169.8

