**Fig 5 pone.0328211.g005:**
[figure not shown]
Interaction Plot of Delta Spectral Power by Condition and Facilitator. This figure illustrates the mean delta spectral power (y-axis) across five experimental conditions – Silence1, NoteA, Silence2, Song, and Silence3 (x-axis) – for the four facilitators ([name], Mother, Father, and [name]). Error bars represent the standard deviation (SD) of individual measurements, highlighting the variability of infants’ responses within each facilitator’s group.

More specifically, we realized that mostly during the ‘NoteA’ condition (as also observed in most of the other conditions), there was a significant increase in Delta Spectral Power for the ‘mother’ facilitator, while surprisingly, the ‘Song’ condition showcased the highest impact particularly for the ‘father’ facilitator. As far as the ‘female music therapist ([name])’ facilitator is concerned, the most stable and lowest Delta Spectral Power across all conditions was observed, indicating a consistent but minimal impact, while the ‘male music therapist ([name])’ facilitator showed moderate variability with minor peaks during the ‘NoteA’ and ‘Song’ conditions. Please note here, that especially for the ‘Song’ condition, the ‘male music therapist ([name])’ facilitator ranked second in impact after the ‘father’ facilitator. To further clarify these specific differences, post-hoc comparisons using the Least Significant Difference (LSD) test were conducted as previously decided, revealing that Delta brain activity was significantly higher with the ‘Mother’ facilitator compared to ‘[name]’ (M = 575.92, *p* = 0.002), ‘[name]’ (M = 409.96, *p* = 0.025), and ‘Father’ (M = 313.55, *p* = 0.085) – although for this latter coming quite close to being significant. Additionally, the ‘NoteA’ condition elicited significantly higher brain activity than the ‘Silence2’ condition (M = 470.26, *p* = 0.022) and showed close trends towards significance when compared to the ‘Silence1’ (M = 323.06, *p* = 0.112) and ‘Song’ conditions (M = 362.86, *p* = 0.075).

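### The abstract's per-condition ranking and two therapist descriptions in the results text disagree with Table 2, and silent-block values are credited to maternal singing

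*Protocol article*

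**What the plan says.** The Abstract summarises the preliminary data from five infants by saying that "maternal singing elicits the highest delta spectral power in all measured conditions except during the" lullaby. For the lullaby it gives a different order, "where paternal singing elicits the highest effects followed by the male music therapist and then the mother".

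The Primary outcomes text that follows Fig 5 describes the two therapists. For the female therapist, "the most stable and lowest Delta Spectral Power across all conditions was observed". The male therapist "facilitator showed moderate variability with minor peaks during the" NoteA and Song conditions.

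The figures behind these sentences are in Table 2 ("Descriptive statistics for spectral power on delta frequency"), which gives the mean, SD and coefficient of variation for each facilitator in each condition. The Intervention section fixes the sequence within a session as Silence1, NoteA, Silence2, Song, Silence3, and labels the three silences Baseline1, Baseline2 and Baseline3.

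**The concern.** Delta spectral power is the primary outcome, and the abstract sentence is its headline result. Many readers will see only that sentence. It has two faults: it names one condition too many, and it presents the values as a response to singing when most of the mother's leads occur in silence. A reader would conclude that maternal singing raises delta power almost everywhere. The table shows instead that the mother's sessions already had the highest mean before she sang.

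The therapist sentences raise a similar issue. Peaks in the two singing blocks suggest that the male therapist's singing produced a response, and his row of Table 2 does not show that pattern. The article offers itself as a methodological template, so its text should agree with its own table.

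**Working it through.** **Which row is which.** The therapist names are masked in the copy reviewed. The results text ranks the male therapist second after the father in Song, which is the row with 270.2. The other masked row (Song 79.1) is therefore the female therapist.

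**Is Table 2 sound?** Averaging the five condition means per facilitator gives:
- Female: (276.1 + 92.7 + 114.8 + 94.3 + 79.1)/5 = 131.4 (Table 3: 131.442)
- Father: 1968.8/5 = 393.8 (393.818)
- Male: 1486.8/5 = 297.4 (297.398)
- Mother: 3536.5/5 = 707.3 (707.362)

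Averaging over facilitators gives condition means of 647.0, 324.0, 176.8, 480.2 and 284.2, against printed totals of 647.1, 324, 176.8, 480.2 and 284.2. SD/mean returns every printed coefficient of variation to within 0.1 point. The table is internally consistent, so the discrepancy lies in the text.

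**Means in delivery order (μV²).**

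| Condition | Mother | Father | Male therapist | Female therapist | Highest | Lowest |
|---|---|---|---|---|---|---|
| Silence1 | 703.1 | 161.2 | 339.0 | 92.7 | Mother | Female |
| NoteA | 1381.3 | 657.1 | 273.6 | 276.1 | Mother | Male |
| Silence2 | 218.0 | 148.7 | 225.7 | 114.8 | Male | Female |
| Song | 213.4 | 574.2 | 270.2 | 79.1 | Father | Female |
| Silence3 | 1020.7 | 427.6 | 378.3 | 94.3 | Mother | Female |

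**1. Mother.** She is highest in three of five conditions. The Silence2 rows are "Mother Silence2 218 168.8 77.4" and, for the male therapist, "Silence2 225.7 137.3 60.9". The gap is 225.7 − 218.0 = 7.7. With five infants per cell (100 observations over 20 cells), the unpaired standard error is √[(137.3² + 168.8²)/5] ≈ 97. The ranking is wrong as printed, but the difference carries no information.

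Of her three leads, NoteA is a singing block and Silence1 and Silence3 are silent. Silence1 comes before any singing in the session. Her lead there is 703.1 − 339.0 = 364.1, with unpaired standard error √[(745.9² + 308.7²)/5] ≈ 361. This does not establish a true baseline difference. It does show that the descriptive lead is present before the stimulus.

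**2. Female therapist.** She is lowest in four of five conditions. The exception is "NoteA 276.1 269.9 97.7" against 273.6 for the male therapist. The gap is 2.5, with unpaired standard error √[(269.9² + 129.5²)/5] ≈ 134.

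Stability depends on the measure:
- *Absolute within-cell SD.* Hers is the smallest of the four facilitators in Silence1 (83.4), Silence3 (84.6) and Song (76.2). It is not the smallest in NoteA (269.9 against 129.5 for the male) or Silence2 (162.3 against 103.3 for the father and 137.3 for the male).
- *Spread across condition means.* Hers run from 79.1 to 276.1, a ratio of 276.1/79.1 = 3.5. The male therapist's run from 225.7 to 378.3, a ratio of 378.3/225.7 = 1.7. The SD of the five means divided by their average is 81.9/131.4 = 62% for her and 60.7/297.4 = 20% for him.

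**3. Male therapist.** In delivery order his means are 339.0, 273.6, 225.7, 270.2 and 378.3: down to Silence2, then up. NoteA is 65.4 below the silence before it. Song is 44.5 above the silence before it (270.2/225.7 = 1.20) but 108.1 below the silence after it. Neither is a peak. They rank third and fourth of five.

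**Do the tests depend on these sentences?** No. The LSD standard error from the reported scale is √(2 × 404,270.98/25) ≈ 179.8. The reported differences 575.92, 409.96 and 313.55 give p = 0.002, 0.025 and 0.085 on 88 df, as printed.

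**The case against.** The strongest reply is that little of substance changes. These are preliminary descriptive data from five infants, labelled as such. The two ranking errors rest on gaps of 7.7 and 2.5, far inside the noise, and the facilitator test and pairwise comparisons do not use the disputed sentences. All of that stands, and it limits the weight of the point.

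Several stronger readings are tempting, and the document does not support them:
- *The facilitator ranking as a whole is misstated.* It is not. The overall order in Table 3 (mother, father, male therapist, female therapist) and the order within Song (father, male therapist, mother) are both right.
- *The abstract hides that the mother leads in only one of the two singing blocks.* It does not; it names the lullaby as the exception. Its one ranking error is Silence2.
- *The male therapist's response is the reverse of the one described.* This goes too far. Song is above the silence that immediately precedes it, which the article designates Baseline2. What fails is the word peaks.
- *The female therapist is not the most stable.* The article does not define stability, and the Fig 5 caption says the error bars are SDs. On that measure the description holds in three of five conditions.

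An after-effect of singing in Silence3 is conceivable, since that block follows both singing stages. The article nevertheless labels it a baseline, and this defence cannot apply to Silence1.

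The masking does not rescue the text. With the two masked rows exchanged, a therapist still exceeds the mother in Silence2, neither row is lowest throughout, and neither row peaks in both NoteA and Song.

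**Conclusion.** The point holds in limited form. Three statements disagree with Table 2, which is itself consistent.
- The mother leads in three of five conditions, not four. Two of the three are silent blocks, one of them before any singing, so these leads cannot be presented as elicited by her singing.
- The female therapist is lowest in four of five conditions, not all, and the stability claim needs a named measure.
- The male therapist has no peak in NoteA or Song.

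The attribution of silent-block values to singing matters most, because it affects how the headline on the primary outcome is read. The ranking slips are trivial in size. No test, overall ordering, sample size or planned analysis is affected. The standard errors above assume five infants per cell and ignore pairing within infant, because the within-infant correlation is not given. The counts of leads and lows need no such assumption.

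**What to change.** - Abstract: say that the mother's sessions had the highest mean delta power in NoteA, Silence1 and Silence3, and that her lead was already present at Silence1. Do not describe values from silent blocks as elicited by singing. Keep the Song order as it is.
- Results text, female therapist: change the claim to lowest in all conditions except NoteA. Either name the measure of stability and limit the claim to the conditions where it holds, or delete it.
- Results text, male therapist: delete the statement about peaks in NoteA and Song. If a description is wanted, say that his highest means were in Silence3 and Silence1 and that Song was above the preceding Silence2.

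The cost is a few corrected sentences and no reanalysis. The maternal headline becomes more modest.

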## Introduction

In the evolving landscape of neonatal neurology, the focus has increasingly shifted towards understanding the complex interplay between the environment and the developmental outcomes of neonates, especially those in critical care settings [1–3]. Globally, a significant number of newborns (just over 13 million) are born prematurely, and many of these vulnerable infants spend their early, formative days in Neonatal Intensive Care Units (NICUs) [4]. Advances in neonatal medicine have dramatically improved the survival rates of these infants [e.g., 5, 6] yet challenges persist in ensuring their long-term neurological health and development. Emerging evidence indicates that prematurity is associated with a heightened risk for enduring neurological and cognitive impairments – including motor deficits, attention difficulties, and behavioral challenges – that may impact academic achievement and quality of life well into adolescence and adulthood [7,8].

Structured sound interventions, approached as non-pharmacological supplementary treatments, have shown promise in improving health outcomes for this vulnerable population in the context of the NICU. For example, white noise has been found to mimic the intrauterine environment, aiding in the stabilization of sleep patterns and reducing stress responses in premature infants [9]. The use of heartbeat sounds has also been instrumental in providing a rhythmic and familiar auditory stimulus to these infants, facilitating physiological regulation and promoting a sense of security [10,11]. Similarly, environmental sounds, such as gentle rain or soft wind, have been shown to create a soothing and more natural auditory environment, contributing to the reduction of the clinical and mechanical noise of the NICU [12–14]. Finally, music – the highest and most complex form of structured sounds, offered via music medicine or music therapy sessions (for a distinction between the two see [15]) – has been widely documented to enhance infants’ physiological and emotional well-being [16–18], with studies demonstrating the respective positive effects on stress reduction, pain management, and weight gain (for example see [19–22]).

### Delivering (live) music interventions in the NICU

While NICUs are pivotal for medical care, they also introduce infants, especially the premature ones, to unique sensory environments [23–25]. These environments differ significantly from the acoustical environment of the mother’s womb or the typical domestic environment, and can profoundly influence developmental processes [26–28]. Therefore, the prescription and implementation of music in NICUs should adhere to tailored and sensitive intervention protocols based on well-studied [29] and biology-based facts [30] to avoid disrupting the developmental trajectory of the infant and potentially act as a developmental catalyst.

For instance, regarding the administration of any sound stimulus in the NICU context, careful moderation is expected to prevent overstimulation and ensure the maintenance of physiological stability in neonates. The extreme sensitivity of premature infants to auditory stimuli necessitates that all sound related stimuli in the NICU should adhere to certain acoustical regulations as defined by specific regulatory medical bodies or global standards [31,32]. These regulations are designed not only to prevent adverse fluctuations in vital signs such as heart rate and respiration – ultimately resulting in stress responses in the infant – but also to optimize the therapeutic benefits of environmental and intentionally administered sound stimuli. Additionally, they aim to minimize potential disruptions to proper biomechanical development, such as damage to the hair cells in the infant’s inner ear. These specialized ear cells are very sensitive to apoptosis events and can take place due to excessive sound stimulation [33–35].

Furthermore, the timing of sound-related interventions should be strategically planned not only to align with each infant’s individual feeding and sleep-wake cycles [36] – as these factors can potentially interfere with the beneficial effects of musical interventions – but also to ensure they occur during quieter periods in the NICU, allowing for safe and effective delivery [14]. In particular, live singing interventions must be carefully calibrated and monitored to stay within safe sound limits set by medical regulations (see [32]). These regulations generally stipulate that sound levels outside the incubator should not exceed a continuous average of 45–50 dB, with transient peaks not surpassing 65 dB. Unfortunately, even highly trained professional singers, when attempting to maintain the lowest possible sound pressure levels (SPLs), may still exceed these limits. A study by Akerlund & Gramming [37] found that trained female singers could only produce minimum SPLs around 51.5 dB at low pitches, which already slightly exceeds the upper recommended continuous sound level in NICUs.

Finally, a seamless integration of any musical intervention into the infants’ overall care regimen requires close coordination with the medical team, as this collaborative effort is vital for aligning the intervention sessions with the already established medical protocols and tailoring them to meet the specific health requirements and medical conditions of each infant [38]. Such integration helps to ensure that the music intervention sessions are not only safe but also effectively support the broader therapeutic goals set forth by the healthcare providers, which especially in this sensitive and demanding in terms of physical development context require the parental involvement as another critical aspect according to the latest clinical research [39,40].

### The role of kinship in the NICU singing process

Prematurity poses significant risks to child development on social, behavioral, and cognitive levels [41]. Most importantly, the early bond between the biologically related caregiver and the infant is crucial for the latter’s cognitive development, influencing the child’s self-representation and future interpersonal relationships [42–43]. However, in the NICU, the typical biological processes of feeding, caring, and bonding are often disrupted due to the infant’s medical complexities, leading to stress for both infants and parents [44].

Parental-infant bonding issues are prevalent among parents who have undergone significant trauma, impairing their sensitivity towards their baby and heightening their vigilance about the baby’s condition [45–48]. Research indicates that premature infants often exhibit more passive behavior, less positive affect, and reduced facial expressions during their interactions with their biological caregivers [49]. Correspondingly, parents of premature infants tend to be less sensitive in these interactions, negatively impacting the infant’s developmental trajectory [50–51]. Conversely, sensitive caregiver attitudes and parent-infant synchronization during interactions have been shown to be protective and beneficial for the development of premature infants [51–53].

In this context, singing can serve as a parent-infant synchronization intervention, fostering emotional bonds and providing comfort to both infants and their parents [54–55]. Additionally, singing in the NICU can stabilize an infant’s physiological state, including heart rate and breathing, and promote better sleep patterns [56–57]. It can also serve as a conduit for emotional expression and connection, offering a sense of normalcy and control for parents who might otherwise feel helpless in the highly medicalized environment of the NICU. As a result, through singing, parents can engage in meaningful interaction with their infants, reinforcing their role as primary caregivers and fostering secure bonding and attachment [58–59].

However, parents are not the only caregivers in the NICU, and for this reason they are not the only ones who may be able to provide singing sessions. Multiple research studies have shown that caregivers with no immediate kinship – like nurses, physicians and other clinical staff – can also effectively use singing to support developmental and medical outcomes [60]. This dynamic is, of course, complex and influenced by factors such as the differentiation of kinship and the recognizability of the caregiver’s voice. The fundamental frequency of their voice, which differs from that of the mother and father, may be less familiar to the infant [61–63].

### The fundamental frequency of singing

In the context of the NICU, understanding the technical features of the singing voice, including its fundamental frequency (F0) as distinct from pitch, becomes increasingly vital, not only due to the auditory sensitivity of premature infants but also because of the developing nature of their central nervous system, which is highly susceptible to the variability of external stimuli as they grow older.

The fundamental frequency (measured in Hertz) refers to a physical property of sound waves – specifically, the number of vibrations per second produced, for example, by the violin string or, in our case, the vocal cords [64–65]. Pitch, on the other hand, is the perceptual correlate of fundamental frequency; it describes how the brain interprets and perceives the fundamental frequency [64]. While F0 is an objective measurement, pitch is a more subjective experience; however, for most periodic sounds, the fundamental frequency closely corresponds to the perceived pitch [64–65]. As a result, F0 is often used as a proxy for pitch in acoustic analysis and research.

Given the critical role of fundamental frequency (F0) in shaping the auditory environment for infants, particularly in a singing context, it is important to understand the differences in F0 between male and female voices. These differences, driven by anatomical factors such as the length of the vocal tract and the size of the laryngeal cavities, result in male voices typically having a lower F0 – around 100–120 Hz – compared to the higher F0 of female voices, generally in the 200–220 Hz range [66–68]. Such distinctions may influence how infants respond to structured sound stimuli, especially in light of the well-documented human sensitivity to voice discrimination based on biological sex [69]. The fundamental frequency serves as the foundation upon which harmonic structures are built, guiding the singing experience and creating a scaffold for the infant’s brain to process the embedded complex auditory information. These differences in F0, therefore, may not only influence how infants respond to the singing environment in the NICU but may also convey biological and kinship-specific cues that can affect neural functioning and development in this sensitive population.

